## Abstract

**Background:**

Non-communicable diseases (NCDs) have reached epidemic proportions in Pacific Island countries. Unhealthy lifestyle is one of the major risk factors and lifestyle interventions have been shown to be efficacious for primary, secondary and early tertiary prevention. However, there is a paucity of evidence regarding effective community-based lifestyle interventions in the Pacific Islands. The Complete Health Improvement Program for high-income countries was contextualised for rural communities with relatively low-literacy rates in low-income countries using the REFLECT delivery approach. This study will assess the effect of this ‘Live More’ program to reduce participant’s NCD risk factors and improve lifestyle behaviours associated with health and wellbeing, in low-literacy communities in countries of the South Pacific.

**Methods/Design:**

This study is a 6-month cluster-randomised controlled trial of 288 adults (equal proportions of men and women aged 18 years and over) with waist circumference of ≥92 cm for men and ≥80 cm for women in four rural villages in each of Fiji, Vanuatu and Solomon Islands. Participants will permanently reside in their village and be able to prepare their own meals. Two villages will be randomised to the ‘Live More’ intervention (*n* = 24) or to control receiving only country specific Ministry of Health literature (*n* = 24). Intervention participants will meet three times a week in the first month, then once a week for the next two months and once a month for the last three months. Themes covered include: NCDs and their causes; and the benefits of positive lifestyle choices, positive psychology, stress management, forgiveness and self-worth, and how these influence long-term health habits. Outcome assessments at baseline, 30-days, 3-months and 6-months include body mass index, waist circumference, blood lipids, blood pressure and blood glucose. Secondary outcomes include changes in medication and substance use, diet, physical activity, emotional health and supportive relationships, collected by lifestyle questionnaire at the same time points.

**Discussion:**

This is the first lifestyle intervention using the Reflect approach to target NCDs. The findings from the study will be used to guide broader delivery of a lifestyle intervention to improve health and wellbeing across the South Pacific.

**Trial registration:**

Australian New Zealand Clinical Trials Registry ACTRN12614001206617.

## Background

Until recently, non-communicable diseases (NCDs), also referred to as ‘chronic diseases’, were viewed as a problem of high-income countries while communicable diseases were the major threat to health in Low and Middle Income Countries (LMICs). However, on a global scale the shift from communicable to NCDs as the major cause of mortality [1] is now complete, with NCDs being responsible for 63 % of all deaths worldwide [2]. In fact, the impact of NCDs is now felt most strongly in LMICs [3] which bear 86 % of the global burden of premature deaths from NCDs [4]. Further, many LMICs now face a double burden of disease from communicable and non-communicable risks [5, 6] resulting in significant social disadvantage and economic burden on individuals, families and society at large [3]. It is projected that as a consequence of NCDs LMICs will accumulate economic losses of US$7 trillion over the next 15 years and produce millions of people trapped in poverty [4].

The four main NCDs are cardiovascular diseases (CVD), cancer, chronic respiratory diseases and diabetes. Diabetes in particular is increasing to epidemic proportions, with 387 million people in the world living with the condition and it was responsible for 4.9 million deaths in 2014 [7]. Eighty percent of people with diabetes live in LMICs, and the Western Pacific (which includes the South Pacific) is seen as the epicentre of the diabetes epidemic [7]. The situation in the South Pacific Islands is particularly alarming with seven of the top ten countries in the world with the highest prevalence of diabetes being Pacific Islands [7]. In Vanuatu, almost 1 in 4 (24 %) of the population have diabetes, and there are similar trends in other Pacific Island countries [7].

The urgency and need to address NCDs in LMICs through appropriate prevention and treatment has only recently been recognised by the United Nations (UN), governments and the non-government organization (NGO) sector [3]. At the 42nd Pacific Islands Forum Communique in 2011, it was declared that ‘NCDs have reached epidemic proportions in Pacific Island countries and territories and have become a human, social and economic crisis requiring an urgent and comprehensive response’ [3]. Clearly, there is a need for effective and relevant programs to address NCDs, particularly in the South Pacific [3, 4]. Unhealthy lifestyle is one of the major risk factors of NCDs [8] and lifestyle interventions have been shown to be efficacious for their primary, secondary and early tertiary prevention [9–13]. However, there is a paucity of evidence regarding effective community-based lifestyle interventions in the Pacific Islands [14].

The Complete Health Improvement Program (CHIP) is a community-based lifestyle intervention that originated in the United States of America and has demonstrated significant benefits for the management of cardiovascular disease [13, 15, 16], type 2 diabetes mellitus [13] and depression [17, 18]. The positive health outcomes have been documented and published in more than 25 peer reviewed journals [19]. CHIP is a holistic, evidence-based, education program which addresses various aspects of health including nutrition, physical activity, substance use, stress, self-worth and happiness [19]. The CHIP intervention involves 18 one to 1.5-h group sessions over 6 to 12 weeks.

While the program was developed for middle to high socio-economic (SES) groups in the United States, recent studies from other high-income countries, such as Australia/New Zealand and Canada [20, 21] have shown similar levels of effectiveness, despite the inherent cultural differences. In addition, CHIP delivered to free-living residents of Appalachia, a lower SES community in the Athens County which struggles with the highest poverty levels in Ohio, produced similar results to those observed in higher SES groups [22].

There have been no published studies of the effectiveness of the CHIP intervention in the Pacific Islands to date, however, unpublished data from large urban centres of the Solomon Islands, Vanuatu and Fiji shows positive biometric outcomes following the program. Noting these pilot findings and the considerable literature supporting the effectiveness of the CHIP intervention, an Australian NGO, the Adventist Disaster and Relief Agency (ADRA) Australia, sought to use the CHIP intervention to address the high rates of NCDs in the Pacific Islands. However, it was recognised that the program was less suited to the rural and most marginalised parts of the Pacific Islands, as well as other LMICs, because: to engage with the program required English literacy, the content was not culturally identifiable, ingredients for suggested recipes were not available, and the program required technical equipment that was not commonly accessible such as video projection. As a result, a contextualised version of the CHIP intervention, appropriate for rural communities with relatively low literacy rates, was developed. The program communicated the core messages embedded in the conventional CHIP but also focused more widely on food security, availability, access and utilisation.

The developed program was built on a model of adult learning and social change known as Regenerated Freirean Literacy through Empowering Community Techniques (REFLECT). The REFLECT model fuses the theories of Brazilian educator Paulo Freire with Participatory Methodologies (PMs) and was developed in the 1990s to link adult literacy to empowerment [23]. Today, the REFLECT approach is used by over 500 organisations in more than 70 countries worldwide [24]. REFLECT utilises a “Reflect Circle” which is a group methodology in which the teacher facilitates discussion, rather than lectures to a ‘class’. The groups meet regularly to discuss local issues and how these can be addressed, while at the same time developing literacy skills. Key to the REFLECT approach is creating a space where people feel comfortable to meet and discuss issues relevant to them and their lives. This is often the first opportunity the village members have to conduct a systematic analysis of their lives and environment. While this process may lack in technical expertise, it is enriched by the local specificity and the connections and insights that emerge, which would not be elucidated by a more formal education process.

ADRA has been using the REFLECT approach to enact social change, financial security and literacy/numeracy in countries such as Tanzania, Albania, Sudan and Cambodia. Anecdotally, these programs have resulted in perceived health and wellbeing benefits, despite not specifically addressing these domains. Hence, it was rationalised that the REFLECT approach might be appropriate for delivering a program specifically targeting NCDs.

This paper provides the rationale and methods for the study of the adapted version of the CHIP intervention, contextualised for low SES communities in the islands of the South Pacific, utilising the REFLECT approach of delivery. The program is referred to as ‘Live More’ and is designed to reduce participant’s NCD risk factors and improve lifestyle behaviours associated with health and wellbeing.

## Methods/Design

### Study design

The ’Live More’ program will be evaluated using a cluster randomised controlled trial. The study design is illustrated in Fig. 1. The 6-month intervention will be conducted in three Pacific Island countries: Solomon Islands, Vanuatu and Fiji. In each country there will be two intervention villages and two control, resulting in a total of six intervention villages and six control villages across the three countries. Assessments will be conducted at baseline, and repeated at 30 days, 3 months and 6 months post baseline. The design, conduct and reporting of this study will adhere to the Consolidated Standards of Reporting Trials (CONSORT) guidelines for group trials.

**Fig. 1 Fig1:**
[figure not shown]
Study design and flow

### Ethical approval

The study was approved by the (name of the ethics committee removed for blinding) Human Research Ethics Committee in New South Wales, Australia (ID: 2014/03) on 18th of March 2014. The protocol for the study is registered with the Australian New Zealand Clinical Trials Registry (ID: ACTRN12614001206617).

### Setting

The local ADRA supervisor will meet with the chiefs/community elders of rural/semi-rural villages within 2 h drive of Honiara in the Solomon Islands, Port Vila in Vanuatu and Suva in Fiji to outline the program and gauge interest.

### Village eligibility criteria and randomisation

A village will be eligible to participate in the study if there is:an expressed endorsement and positive commitment by the village chief/community leader;observable overweight in the community (estimation of at least 40 % as observed by the ADRA Supervisor);relatively low literacy rate/education level in the potential participants as indicated by the community leader;adequate interest by residents who meet the participant eligibility criteria (described below) to achieve the required cluster sample size (described below);willingness to participate in the study as either a treatment or control site.

Once eligible villages are identified, ensuring they are not in immediate proximity to each other to avoid cluster contamination, the villages in each country will be randomised to either intervention or control by a researcher not familiar with the geographic location or nature of the village. Figure 1 shows the sequence for allocation of sites to treatment and control conditions.

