### Participant recruitment and eligibility criteria

Participants will be recruited through a village meeting called by the village elder. During this meeting, an ADRA Supervisor together with a designated health professional (HP-doctor or nurse) will provide information about the program. Following the information session, a call for volunteers who meet the eligibility criteria will be made. To be considered eligible to participate in the study the individuals will:be 18 years of age or older;live permanently in the village (for the duration of the program)have a waist circumference of ≥92 cm for men and ≥80 cm for women (as levels at and above these are indicative of risk of NCD) [25];be prepared to engage in the ‘Live More’ intervention and monthly post-program meetings (total duration of 6 months);be able to provide their own meals (because this will enable compliance with the program’s dietary recommendations).

An equal number of males and females will be recruited for the study. No payments will be requested of participants and the participants will not receive any financial remuneration for their involvement.

Individuals will be considered ineligible to participate in the study if they meet one or more of the following exclusion criteria:unstable angina;myocardial infarction within the previous 12 months;coronary by-pass surgery within the previous 12 months;other medical contraindications for dietary change or increased physical activity, as determined by the HP;chronic infectious disease/s, as participants illness may affect participation in the program;are a direct relative of the village chief (to reduce bias in recruiting).

All eligible participants will be explained the consent process, and informed that all personal information will be confidential and anonymous. They will then be asked to sign or make their mark on the consent form or give the appointed HP for the study verbal consent to sign on their behalf in the presence of a witness (in case of literacy constraints).

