### Program facilitators

Community leaders of the respective intervention villages will propose one eligible candidate of each gender from the local village to act as facilitators of the program. To be considered eligible the potential facilitator must: have completed secondary education, be fluent in English, be respected in the village, be a non-smoker, and have an interest in health and desire to positively impact the health of their village. ADRA Australia will provide the local village facilitators with two weeks of training using Strength Based [26–28] and Appreciative Inquiry (AI) approaches. The training sessions will cover the principles of the CHIP intervention and the REFLECT methodology, as well as the development of facilitation skills and the research methods used in the study.

Following the training, the local ADRA supervisor together with the facilitators from the study villages will collaborate with ADRA Australia and the local ADRA office to ensure a Facilitators Manual (including 18 lesson plans) meet the local context. Following the 6-month program, this collaborative process will be repeated to further contextualise the Facilitator Training and Process Manual’s for the Pacific. The local ADRA supervisor will be responsible for follow up, mentoring the village facilitator and monitoring the program and research.

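### The protocol does not place volunteering, screening and consent before disclosure of the village's arm, and it requires every participant, controls included, to be ready to engage in the intervention.

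*Protocol article*

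**What the plan says.** **Allocation.** Under Village eligibility criteria and randomisation, the sequence begins "Once eligible villages are identified, ensuring they are not in immediate proximity to each other to avoid cluster contamination"; then "the villages in each country will be randomised to either intervention or control by a researcher not familiar with the geographic location". Two of the conditions a village must meet beforehand bear on this point: "adequate interest by residents who meet the participant eligibility criteria (described below) to achieve the required cluster sample size" and "willingness to participate in the study as either a treatment or control site". The section refers to Figure 1 for the allocation sequence; that figure is not reproduced in the text available.

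**Recruitment.** Under Participant recruitment and eligibility criteria, "Participants will be recruited through a village meeting called by the village elder". A supervisor and a health professional present the program. "Following the information session, a call for volunteers who meet the eligibility criteria will be made". Among the criteria, each person must be ready to engage in the Live More "intervention and monthly post-program meetings (total duration of 6 months"). There is one list of criteria for both arms. Eligibility also depends on a waist measurement and on exclusions that the health professional judges.

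**Facilitators.** Under Program facilitators, "Community leaders of the respective intervention villages will propose one eligible candidate of each gender from the local village". Those nominated receive two weeks of training, and work on the manual follows.

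**Timetable and control arm.** Table 1 (Intervention) puts baseline measurement at week 0 and sessions 1 to 3 in week 1. Under Control villages, Ministry of Health literature is given out at the first health screening.

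**The concern.** In a cluster trial, randomising villages protects the comparison of villages. It protects the comparison of people only if the people are identified before anyone who influences enrolment knows the arm. Here enrolment is by self-selection at an open meeting, which is the step most exposed to known allocation. Someone who hears that the village will receive a six-month programme with local facilitators has different reasons to volunteer from someone who hears that it will receive printed literature.

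Motivation is likely to affect diet, activity and attendance, the routes by which the programme is meant to act. It is not among the measurements listed under Outcome measures, so later adjustment could not use it directly, and six villages per arm give little scope for adjusting at village level. The authors do recognise recruitment bias, since they exclude direct relatives of the village chief for that reason, but this route is left open.

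**Working it through.** No stated figure is in dispute. The check is one of sequence, made by setting the sections side by side.

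1. **What triggers randomisation?** Village eligibility. The nearest that condition comes to enrolment is enough interest among residents who meet the criteria. Consent, waist measurement and the health professional's exclusions are not part of the trigger.

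2. **When must the intervention villages know their arm?** Only leaders of intervention villages nominate facilitators, so nomination comes after allocation is known to them. Training takes two weeks and adaptation of the manual follows. Sessions start in week 1, so training must begin no later than about week 1 − 2 = week −1, and earlier once the manual work is counted. Baseline is at week 0. On the protocol's own schedule, the intervention village, its leader and the supervisor therefore know the arm before baseline.

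3. **When do control villages and their assessors know?** No later than the first health screening, because the literature given out there goes only to controls. The text does not say whether the waist criterion and the judged exclusions are applied on that same occasion. If they are, the person deciding eligibility knows the arm.

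4. **Where do the meeting, screening and consent fall relative to steps 1 to 3?** The text does not say. It also does not say that recruiters or residents are unaware of the arm. The unfamiliar researcher conceals the assignment of villages, not the recruitment of individuals.

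5. **Does the willingness criterion fit both arms?** No. If people do not know their arm, they should be asked about willingness for either. If they do know it, the criterion has no content for controls. The protocol sets the either-arm standard for the village but does not carry it to the individual.

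**Scale, as illustration only.** The documents give no estimate of differential selection. Inputs from the Power calculation section: triglyceride SD 0.33 mmol/L, 87 participants per country over two arms (43.5 per arm), 5% significance, 80% power. No effect size is stated. Assuming a two-sided test and ignoring clustering, the detectable difference is 0.33 × (1.960 + 0.842) × √(2/43.5) = 0.198 mmol/L. If selection shifted prognosis by an assumed 0.1 to 0.2 SD, that would be 0.1 × 0.33 = 0.033 to 0.2 × 0.33 = 0.066 mmol/L, or 0.033/0.198 = 17% to 0.066/0.198 = 33% of the detectable difference. The shift is an assumption, and the planned analysis is of change from baseline, so a shift in prognosis need not carry over one-to-one.

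**The case against.** A reader might infer that volunteers are recruited after their village has been randomised. The document does not establish this. No sentence gives the order, the sections of an article are arranged by topic, and the missing figure may show it. Two conditions point partly the other way. The interest requirement implies that residents were approached, and to some extent matched to the criteria, before allocation. The village must also accept either arm. A single participant list is consistent with volunteers who do not yet know their arm.

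A reader might also infer that facilitators have already been nominated when volunteers come forward. The timetable places nomination before baseline, but not before the village meeting.

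The 17% to 33% above might be read as an estimate of bias. It is not one, because it rests on an assumed shift and on a detectable difference that the protocol does not state.

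Finally, a condensed article may leave details of disclosure to the full protocol, and moving baseline ahead of facilitator training would disturb Table 1, where assessments are timed from baseline.

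These objections rule out a claim that randomisation has been breached, and they shape the remedy. They do not remove three facts: the stated trigger is village eligibility, the schedule implies that the arm is known by baseline, and the willingness criterion is written for the intervention alone. Expressed interest is not consent or a closed list, and a village's acceptance of either arm does not speak for its residents.

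**Conclusion.** The point holds as a weakness in what the protocol fixes. Randomisation is tied to village eligibility rather than to a completed participant list. The arm is known by baseline on the protocol's own schedule, nothing in the available text secures recruitment before disclosure, and the individual willingness criterion does not suit a two-arm trial whatever the order. Differential recruitment is therefore a real risk, conditional on recruitment following disclosure. Its size cannot be known from the document.

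The conclusion rests on reading Table 1 and the two-week training period literally, and on the missing figure not settling the order. If the figure or the full protocol shows consent and screening complete before disclosure, only the criterion's wording remains to be corrected. The change is worth making because it is cheap and removes a recognised source of bias in cluster trials; confidence is moderate.

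**What to change.** - **Order.** In each country, hold the village meetings, complete eligibility screening (including waist and the health professional's exclusions), obtain consent in all four villages, and close the participant list. Only then draw or disclose the allocation.
- **Facilitators and baseline.** Nominate and train facilitators after disclosure. Keep baseline biometrics and the questionnaire at week 0, so that Table 1 is unchanged.
- **Criterion.** Reword it for everyone as readiness to take part in either the programme or the control condition for 6 months.
- **Reporting.** Count, by arm, anyone on the closed list who does not reach baseline, since that loss would occur after disclosure.

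The cost is small: steps already planned are re-ordered, screening and baseline become separate visits, and a few weeks pass between consent and baseline while facilitators are trained, with possible minor drop-out in that interval.
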